### Sample size calculation

2.4

We aim to assess whether the glucose response to a meal is sufficiently person-specific to use in personalized dietary advice and will determine person-specific responses to meals and food products in the dietary intervention. The person-specific responses will be identified by correlating the glucose response to a meal or food product to the individual’s average postprandial glucose response over the 9-week controlled diet. An example of potential results is depicted in Figure 3. A high correlation would indicate that individuals are likely to respond as expected based on the average glucose response (Figure 3A), so no person-specific response. Low correlations would indicate a person-specific response; for example, individuals with a high average glucose response may have a low glucose response to the meal or food product, and vice versa (Figure 3B).

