**Figure 3 fig3:**
[figure not shown]
Example of expected results regarding postprandial glucose responses to a specific food product related to the individual’s average glucose response. **(A)** A high correlation indicates that postprandial glucose responses to the product are in line with an individual’s average glucose response. **(B)** A low correlation indicates that the postprandial glucose responses to the product deviate from an individual’s average glucose response, suggesting the presence of meal-specific glucose responses.

To estimate the required sample size to be able to detect meal-specific responses, we used preliminary data from 27 participants of the GLYSIMI study (NCT05120661). The GLYSIMI study investigated the role of the human small intestine microbiota in regulating postprandial glucose responses to food products. The study included men and women with a BMI of 25–40 kg/m^2^, aged 40–75 years. During the screening phase of the GLYSIMI study, participants wore a continuous glucose monitor, and glucose responses after seven standardized products at breakfast or dinner were compared. All glucose responses were measured as the iAUC (mg/dl*hour, 120 min postprandially). The average glucose response was calculated as the average glucose response to all products per individual. Correlations between postprandial glucose responses to specific foods and the average postprandial glucose response of an individual ranged between 0.49 and 0.85.

In the RepEAT study, we expect lower correlations between glucose responses to specific food products and the average glucose response, because we measured nine weeks of a fully controlled diet and not only a few standardized meals. Therefore, we expected correlations ranging between 0.3 and 0.4. Using GPower (version 3.1.9.7) and a “Correlation: Point biserial model,” with a two-sided test, an α of 0.05, a power of 0.80, and an effect size of 0.3 and 0.4, this would lead to a required samples size of, respectively, 44 or 82 participants. We chose the average of the two and therefore 57 participants were needed in this study. Considering a 10% drop-out rate, the required sample size was *n*=57 + 6=**63** participants.

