## Statistical analysis

3

Within the RepEAT study, we aim to examine how replicable glucose responses are within individuals and how consistent the variation in glucose responses is between individuals under standardized conditions of a 9-week fully controlled dietary intervention. To determine the replicability of glucose responses to identical meals and food products within individuals, we will compare the three repetitions per meal or food product. To assess the variability in glucose responses to identical meals between individuals, we will compare the three repetitions per product between individuals. Glucose responses will be corrected for metabolic state of insulin sensitivity by using the average glucose response to all meals in the diet and/or the glucose response to the OGTT, and by correcting for physical activity.

IBM SPSS Statistics and the latest R software will be used to carry out the statistical analyses. Numerical values in descriptive statistics will be reported as mean ± SD, categorical values will be reported as numbers and percentages. To determine the normality of the data, a visual inspection of QQ plots and results of the Kolmogorov–Smirnov test will be used. For linear mixed model analyses, model residuals will be checked for normality. Non-normally distributed data will be transformed before the analyses. *p*-values <0.05 will be considered statistically significant.

Glucose responses to single meals will be measured as the incremental area under the curve (iAUC; mg/dl*hour) and will be calculated from the latest timepoint before consumption until 120 min after consumption. In addition, the glucose peak and time to peak will be measured within each postprandial glucose response curve, within 120 min after consumption of a test product. For each meal and food product there will be three repeated measures during the dietary intervention. Glucose responses to single meals will be associated with the average iAUC of all glucose responses of an individual. There will be adjusted for multiple testing using false-discovery rate adjustment according to the Benjamini-Hochberg procedure (32).

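### A low correlation with the person's average cannot by itself show a person-specific response, because occasion-to-occasion noise lowers it too, and the planned replicability check is not tied to it

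*Protocol article*

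**What the plan says.** The Study design section names the person-specific glucose response, measured by 2 h iAUC, as the primary outcome. The Sample size calculation section says how it is found: "The person-specific responses will be identified by correlating the glucose response to a meal or food product to the individual’s average postprandial glucose response", taken over the nine-week diet. It then gives the reading in both directions. "A high correlation would indicate that individuals are likely to respond as expected based on the average glucose response", which the article takes as no person-specific response. At the other end, "Low correlations would indicate a person-specific response". The caption of Figure 3 repeats the second inference for panel B, "suggesting the presence of meal-specific glucose responses".

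The Statistical analysis section plans the same association: "Glucose responses to single meals will be associated with the average iAUC of all glucose responses of an individual". It also says that the three repetitions of each product will be compared, within and between individuals, to assess replicability, and it mentions linear mixed models without specifying one. It does not say that a product must replicate before a low correlation counts as person-specific, and it describes no correction of the correlation for noise.

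The Introduction sets the target: whether individuals replicably respond strongly to certain foods relative to their own average. The Discussion likewise asks whether responses are robust enough for advice.

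**The concern.** The target is a deviation from the person's own average that comes back on repetition. The stated rule looks at something else: how closely a product's responses line up with those averages across people. The alignment is poor if people have stable, product-specific reactions. It is equally poor if the same person's response to the same product changes from one occasion to the next through sensor error or day-to-day variation. Only the first is of use for personal advice.

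Other things equal, a less repeatable product gives a lower correlation and so looks more person-specific under the rule. Because the rule defines how the primary outcome is identified, a reader who applies it as written could draw the main conclusion from noise.

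**Working it through.** **Inputs from the document.** Expected correlations: "Therefore, we expected correlations ranging between 0.3 and 0.4". Pilot: correlations between specific foods and the "average postprandial glucose response of an individual ranged between 0.49 and 0.85" (27 participants, seven products). Three repetitions per product, 378 meals per completer (126 per three-week cycle), 53 completers. No within-person SD, ICC or other reliability is given, so every reliability below is an assumption.

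**The plan's own figure.** The sample size rests on these correlations, "with a two-sided test, an α of 0.05, a power of 0.80, and an effect size of 0.3 and 0.4". The point-biserial calculation gives 82 participants for 0.3 and 44 for 0.4. Both of the article's numbers reproduce, though it lists them in the opposite order, and their average is (82 + 44)/2 = 63 rather than 57. These slips are separate and nothing below depends on them. What matters here is that the calculation tests a correlation against zero. It says nothing about whether a low correlation reflects a reproducible effect.

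**Model.** Write a product's iAUC as person level (variance P) + reproducible person-by-product effect (G) + occasion noise (E). With k repeats averaged and a person average taken over many meals,

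r ≈ √[P / (P + G + E/k)].

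For a single occasion (k = 1), G and E enter identically. No value of r can tell them apart.

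**Expected r with no person-by-product effect (G = 0).** Let the single-occasion reliability be ρ = P/(P + E). Then r = √ρ for one occasion and r = √[3ρ/(1 + 2ρ)] for the mean of three.

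| Assumed ρ | r, single occasion | r, mean of three |
|---|---|---|
| 0.1 | √0.1 = 0.32 | √(0.3/1.2) = 0.50 |
| 0.2 | √0.2 = 0.45 | √(0.6/1.4) = 0.65 |
| 0.3 | √0.3 = 0.55 | √(0.9/1.6) = 0.75 |
| 0.5 | √0.5 = 0.71 | √(1.5/2) = 0.87 |

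Read backwards, for single occasions, the planned 0.3 to 0.4 arises from noise alone at ρ = 0.3² to 0.4² = 0.09 to 0.16. The pilot range of 0.49 to 0.85 arises at ρ = 0.24 to 0.72, ignoring the fact that each product is part of the average. With three repeats averaged, 0.3 to 0.4 would need E = 30.3P to 15.75P, that is ρ = 1/31.3 to 1/16.75, or about 0.03 to 0.06.

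**Opposite truths, similar answer.** Simulation with 53 people, 42 products (assumed), three repeats, and P equal to 10% of single-occasion variance:

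| Remaining 90% of variance | Mean r, single occasion | Correlation between repeats of deviations from the person's average |
|---|---|---|
| All noise | 0.32 | 0.00 |
| Half and half | 0.33 | about 0.5 |
| All person-by-product effect | 0.35 | 1.00 |

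The correlation with the average barely moves. The repeat-to-repeat correlation of deviations, whose expected value is G/(G + E), separates the three cases completely.

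**How often noise alone gives a low value.** The article sets no threshold for low. With r < 0.4 as an illustration only, and G = 0, the share of products below it is:

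| Assumed ρ | Single occasion | Mean of three |
|---|---|---|
| 0.1 | about 72% | about 14% |
| 0.2 | about 30% | about 0.4% |
| 0.3 | about 7% | 0% |
| 0.5 | about 0.1% | 0% |

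**The case against.** The strongest reply is that replicability is already in the plan. The Introduction asks about replicable responses, the Statistical analysis section opens with the comparison of the three repetitions, and the Discussion says that the repeats will be used to judge robustness. A purely noisy product would show up there. The design also limits noise: supplied meals at fixed times and in fixed order, no test products on the day after a sensor change, and correction for physical activity. The article leaves open whether the correlation uses single occasions or the mean of the repeats, and the mixed models that it mentions could include the needed variance component.

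Much of this stands, and it rules out three stronger readings that a reader might infer. First, that noisy products will be reported as person-specific: this follows only if the correlation is read alone, and a separate analysis is planned that would flag them. Second, that the repeats are kept out of the correlation: the text does not say so. Third, that about 72% of products would be falsely labelled: that figure combines the lowest assumed reliability, single occasions and a cut-off that is not the plan's. It is also too much to say that every error favours person-specificity. Noise pushes that way, but a product's share in the person's own average raises the correlation, if only slightly with 378 meals.

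What the reply does not remove is the stated rule. The article says that person-specific responses will be identified by this correlation and gives the meaning of a low value. Nothing makes replication a condition of that reading, and comparing the repetitions separately does not correct the correlation. A product could fail the replicability comparison and still meet the rule. Averaging three repeats weakens the problem but does not abolish it. This is an objection to a rule that the protocol fixes, not to detail left for an analysis plan.

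**Conclusion.** The concern holds in this form: a low correlation with the person's average reflects occasion noise as well as a reproducible person-by-product effect, so the rule cannot carry the person-specific conclusion alone, and the planned replicability comparison is not linked to it. The algebraic point needs no assumed reliability.

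The practical size does, and the document supplies none. It ranges from large (single occasions at reliability 0.1) to negligible (three-repeat means at reliability 0.2 or more). These figures assume additive, independent components with equal noise across products. The document does not show which end of the range applies. The link should be made before analysis begins, because the primary outcome is identified by this rule.

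**What to change.** Define the person-specific response as a replicable deviation from the person's own average. Fit one mixed model to all three repetitions with product as a fixed effect and participant and participant-by-product as random effects. Report the participant-by-product variance against the residual variance, with a confidence interval. The between-repeat correlation of deviations from the person's average serves the same purpose. Report the repeatability of each product alongside.

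If the correlation plot is kept, use the mean of the three repeats and compare each correlation with the ceiling set by that product's reliability, instead of calling it high or low. Reword the Sample size calculation section and the Figure 3 caption so that a low correlation counts as person-specific only where the deviation replicates.

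The cost is one additional model and revised wording. The repeats have been collected, and the Study design section places the project in data cleaning.

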**Figure 3 fig3:**
[figure not shown]
Example of expected results regarding postprandial glucose responses to a specific food product related to the individual’s average glucose response. **(A)** A high correlation indicates that postprandial glucose responses to the product are in line with an individual’s average glucose response. **(B)** A low correlation indicates that the postprandial glucose responses to the product deviate from an individual’s average glucose response, suggesting the presence of meal-specific glucose responses.

To estimate the required sample size to be able to detect meal-specific responses, we used preliminary data from 27 participants of the GLYSIMI study (NCT05120661). The GLYSIMI study investigated the role of the human small intestine microbiota in regulating postprandial glucose responses to food products. The study included men and women with a BMI of 25–40 kg/m^2^, aged 40–75 years. During the screening phase of the GLYSIMI study, participants wore a continuous glucose monitor, and glucose responses after seven standardized products at breakfast or dinner were compared. All glucose responses were measured as the iAUC (mg/dl*hour, 120 min postprandially). The average glucose response was calculated as the average glucose response to all products per individual. Correlations between postprandial glucose responses to specific foods and the average postprandial glucose response of an individual ranged between 0.49 and 0.85.

In the RepEAT study, we expect lower correlations between glucose responses to specific food products and the average glucose response, because we measured nine weeks of a fully controlled diet and not only a few standardized meals. Therefore, we expected correlations ranging between 0.3 and 0.4. Using GPower (version 3.1.9.7) and a “Correlation: Point biserial model,” with a two-sided test, an α of 0.05, a power of 0.80, and an effect size of 0.3 and 0.4, this would lead to a required samples size of, respectively, 44 or 82 participants. We chose the average of the two and therefore 57 participants were needed in this study. Considering a 10% drop-out rate, the required sample size was *n*=57 + 6=**63** participants.

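### The 80% power stated for detecting meal-specific responses is power to reject a zero correlation, and neither outcome of that test establishes the low correlation by which the article defines meal-specificity

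*Protocol article*

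**What the plan says.** Everything needed is in section 2.4 (Sample size calculation) of the protocol article, including the Figure 3 legend.

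- **Purpose of the calculation:** "To estimate the required sample size to be able to detect meal-specific responses".
- **Reading of a high correlation:** "A high correlation would indicate that individuals are likely to respond as expected based on the average glucose response". The article takes this as no person-specific response.
- **Reading of a low correlation:** "Low correlations would indicate a person-specific response". The Figure 3 legend agrees: "A low correlation indicates that the postprandial glucose responses to the product deviate from an individual’s average glucose response". It treats this as a sign of meal-specific responses.
- **Pilot data (27 participants):** "Correlations between postprandial glucose responses to specific foods and the average postprandial glucose response of an individual ranged between 0.49 and 0.85".
- **Planning values:** "Therefore, we expected correlations ranging between 0.3 and 0.4".
- **Test that was sized:** G*Power, "Correlation: Point biserial model", "with a two-sided test, an α of 0.05, a power of 0.80, and an effect size of 0.3 and 0.4". The printed sizes are 44 and 82. The article settles on 57, and on 63 after allowing for drop-out.

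The Results section reports 53 completers and cites the 44 to 82 range in support of that number. The Statistical analysis section says that single-meal responses will be associated with the person's average iAUC, with false-discovery-rate adjustment. It gives no null value for the correlation and no cut-off for what counts as low.

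**The concern.** The section states a purpose and a power figure that point in different directions. The purpose is to detect a low correlation. A standard correlation test entered with effect sizes of 0.3 and 0.4 is a test for a correlation away from zero, and its power grows as the correlation grows. If that is the test behind the 80%, the trial has a power statement for showing that a product's response is related to the person's average, and none for showing that the relation is weak.

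The correlation is not incidental: section 2.4 presents it as the means of identifying person-specific responses and ties it to the overall aim. A reader who takes the 80% at face value would think that the trial was sized for that aim. A non-significant correlation could also be read as support for person-specific responses when it may only reflect limited precision.

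**Working it through.** **Inputs.** From section 2.4: two-sided alpha 0.05, power 0.80, correlations 0.3 and 0.4, point-biserial model, pilot range 0.49 to 0.85. From Results: n = 53 completers. The article does not write out the null correlation, so the first step is to recover it.

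**1. Reproducing the printed sizes.** For the point-biserial model with null ρ = 0, the test statistic follows a noncentral t with n − 2 degrees of freedom and noncentrality δ = √n · ρ / √(1 − ρ²). Power is the probability that |t| exceeds the two-sided 5% critical value.

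- ρ = 0.3, n = 82: δ = 9.055 × 0.3 / 0.954 = 2.85, critical t = 1.990, power 0.803. At n = 81 power is 0.798.
- ρ = 0.4, n = 44: δ = 6.633 × 0.4 / 0.917 = 2.89, critical t = 2.018, power 0.807. At n = 43 power is 0.798.

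The smallest sizes reaching 80% are 82 and 44, exactly as printed (the article lists them in the reverse order of the effect sizes). The powered test is rejection of ρ = 0.

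**2. How that test behaves at n = 53.** The same formula gives:

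| True ρ | 0 | 0.1 | 0.2 | 0.3 | 0.4 | 0.49 |
|---|---|---|---|---|---|---|
| Chance of rejecting ρ = 0 | 5% | 11% | 31% | 61% | 88% | 98% |

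The test is least likely to be significant where meal-specificity, as the article defines it, is strongest. An observed |r| must exceed about 0.27 to reach significance.

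**3. Precision at n = 53.** On the Fisher z scale the standard error is 1/√(53 − 3) = 0.141, so the 95% half-width is 1.96 × 0.141 = 0.277.

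- r = 0.35: tanh(0.365 ± 0.277) = 0.09 to 0.57.
- r = 0.40: tanh(0.424 ± 0.277) = 0.15 to 0.60.

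Both intervals exclude zero, and both reach into the lower end of the pilot range (0.49 to 0.85). They stop well short of its upper end.

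**4. Power for the claim itself.** Showing a low correlation needs a null of the form ρ ≥ ρ₀. The documents give no ρ₀, so 0.5, 0.6 and 0.7 are assumptions, chosen inside the pilot range. With one-sided alpha 2.5%, n = 53 and true ρ = 0.35, power = Φ[(atanh ρ₀ − atanh 0.35) × √50 − 1.96]:

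- ρ₀ = 0.5: Φ[(0.549 − 0.365) × 7.071 − 1.96] = Φ(−0.66) = 0.25
- ρ₀ = 0.6: Φ[(0.693 − 0.365) × 7.071 − 1.96] = Φ(0.36) = 0.64
- ρ₀ = 0.7: Φ[(0.867 − 0.365) × 7.071 − 1.96] = Φ(1.59) = 0.94

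(The z values use unrounded atanh terms.) With the bound at the pilot minimum, 0.49, and true ρ = 0.4, power is about 0.12. With the bound at the pilot maximum, 0.85, it is above 0.99.

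**The case against.** The strongest reply is that the article reads the size of the correlation, not its significance. On that reading a significant r of 0.35, below the whole pilot range, could still be called low, and the test of zero is only a check that the correlation can be estimated usefully. This stands in part. A reader might infer that rejecting ρ = 0 is evidence against meal-specificity. The documents do not support that, because rejection rules out only a correlation of exactly zero. But a reading by size needs a cut-off or a precision target, and the calculation has neither, so the 80% still does not attach to the claim.

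A reader might also infer that the investigators will treat a non-significant correlation as proof of a person-specific response. No part of the article says so. The risk is that it could be read that way, not that this is the planned rule.

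Third, the correlation is not the only evidence planned. The Statistical analysis section also compares the three repetitions of each product within and between individuals and mentions linear mixed models, and a fuller analysis plan may specify a participant-by-product term. This stands, and it confines the point to the sample-size calculation and the claim attached to it.

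Last, a reader might conclude that 53 participants are too few. That does not follow: power for the claim is low or high according to the bound chosen.

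The point-biserial model strictly applies when one variable is binary, whereas both iAUC measures are continuous. A Fisher z calculation gives 85 and 47 instead of 82 and 44. A difference of about three participants is too small to carry any weight here.

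**Conclusion.** The point holds in a limited form. The calculation is offered as power to detect meal-specific responses but gives power to reject a zero correlation. Neither outcome of that test establishes meal-specificity as the article defines it, so the article states no power for that claim. The null of ρ = 0 is an inference, but a firm one, because it returns both printed sizes exactly.

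The consequence lies in what the trial can conclude from this correlation, not in its data or endpoint. At n = 53, power for the claim at a true correlation of 0.35 runs from about 0.25 to 0.94 over assumed bounds of 0.5 to 0.7. These figures rest on the Fisher z approximation, one product tested at one-sided 2.5% without multiplicity adjustment, and bounds that are ours. Even for the test that was sized, power with 53 completers is about 61% at 0.3 and 88% at 0.4, so 80% does not hold across the planning range.

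This should be fixed before analysis. Enrolment is complete, so the calculation can no longer change the sample size.

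**What to change.** Before the glucose responses are analysed:

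1. Describe the 80% as power to detect a non-zero association between a product's response and the person's average, and add that with n = 53 this power is about 61% at ρ = 0.3 and 88% at ρ = 0.4.
2. For the person-specific claim, fix and justify an upper bound for a low correlation and test the null that ρ is at or above it. Alternatively, test whether the participant-by-product variance is zero, using the three repetitions of each product.
3. Report the power or confidence-interval width of the chosen analysis at n = 53.
4. State that a non-significant test of ρ = 0 will not be taken as evidence of a person-specific response.

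The cost is a few sentences in the plan and a short recomputation, with no new data. The article describes the project as being in data cleaning, so the bound can still be set before results are known. The one real piece of work is agreeing and justifying that bound.

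### The sample size powers rejection of r = 0, although a low product–average correlation is the result of interest, and the plan reads a low value as person-specific without allowing for measurement noise

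*Protocol article*

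**What the plan says.** Section 2.4 (Sample size calculation) identifies person-specific responses by correlating the response to a product with the individual's nine-week average. A high correlation means no person-specific response. At the other end, "Low correlations would indicate a person-specific response".

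For the effect size, "we used preliminary data from 27 participants of the GLYSIMI study", in which "glucose responses after seven standardized products at breakfast or dinner were compared". The pilot average included the product under test: "The average glucose response was calculated as the average glucose response to all products per individual". The resulting correlations "ranged between 0.49 and 0.85". The article then expects lower values in RepEAT "because we measured nine weeks of a fully controlled diet and not only a few standardized meals" and concludes: "Therefore, we expected correlations ranging between 0.3 and 0.4". It gives no calculation that leads from one range to the other.

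The power calculation uses a point biserial model, two-sided, with alpha 0.05 and power 0.80. It reports 44 and 82 participants and settles on 57, or 63 with drop-out. Section 4 (Results) reports 53 completers and judges them against the 44–82 range. Section 3 (Statistical analysis) plans to compare the three repeats of each product and, separately, to associate single responses with the average iAUC.

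**The concern.** Three things do not fit together.

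- **The test and the claim point in opposite directions.** The calculation gives power to show that a correlation differs from zero. By the article's own rule, a correlation clearly above zero moves towards no person-specific response. Failing to reject zero would not establish a low correlation either.
- **A low correlation has two causes.** It may mean that a person responds to this product repeatably but out of line with their average. It may also mean that a single two-hour CGM response is noisy. The rule in section 2.4 does not separate them.
- **The planning value is not derived.** It lies wholly below the only data cited.

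At stake is the main conclusion, namely whether responses are person-specific enough for dietary advice. If noise is read as person-specificity, the answer could be yes when the data show only poor repeatability.

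**Working it through.** **Inputs from the article.** Pilot correlations 0.49–0.85, n = 27, seven products, average over all seven; assumed r = 0.3–0.4; two-sided alpha 0.05, power 0.80; 53 completers; 378 meals per completer; three repeats per product.

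**1. The plan's own figure.** Point biserial model: noncentral t with df = N − 2 and noncentrality √(N·r²/(1 − r²)). The smallest N with power at least 0.80 is 82 at r = 0.3 and 44 at r = 0.4. Both figures reproduce. (The text prints them in reverse order, and their mean is 63, not 57. That is a separate matter.)

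**2. What the test would show.** Power to reject r = 0 at 53 completers is:

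| True r | Power |
|---|---|
| 0.30 | 0.61 |
| 0.35 | 0.76 |
| 0.40 | 0.88 |
| 0.49 | 0.98 |

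The higher the correlation, and so the less person-specific the response by the article's rule, the more surely the test succeeds. If correlations resemble the pilot, almost every product will differ significantly from zero, and this tells the reader little.

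**3. Noise alone.** Suppose there is no person-specific response: each response is the person's general level plus noise, and the long average is nearly error-free. Then r = √R, where R is the reliability of a single response. Hence R = r²: 0.3² = 0.09 and 0.4² = 0.16.

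More generally, the error-corrected correlation is r/√R. The documents give no R, so I take a range as an assumption. An observed 0.35 corresponds to 0.35/√0.25 = 0.70 at R = 0.25, and to 0.35/√0.5 = 0.49 at R = 0.5. The same observed value can therefore mean quite different things.

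**4. From the pilot to RepEAT.** With k equally intercorrelated products of equal variance, the correlation of one product with the average that contains it is √((1 + (k − 1)ρ)/k).

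- With ρ = 0 and k = 7 this is 1/√7 = 0.38. With k = 378 it is 1/√378 = 0.05.
- Solving at k = 7 gives ρ = (7r² − 1)/6. For r = 0.49, 0.67 (midpoint of the range) and 0.85, ρ = 0.113, 0.357 and 0.676.
- At k = 378 these become 0.34, 0.60 and 0.82.

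The direction is therefore down, as the article expects, but only the bottom of the pilot range reaches 0.3–0.4. In a simulation with unequal loadings, the weakest product falls from 0.46 to 0.30 and the strongest stays about level (0.79 to 0.80).

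Averaging the three repeats would push the other way. As the share of non-shared variance that is occasion noise goes from 0 to 100%, the pilot's low end projects to 0.34–0.53 and its high end to 0.82–0.93.

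**5. Effect on N for the stated test.** Using the pilot correlations directly, N = 27 at r = 0.49 and N = 6 at r = 0.85. The low assumption raised N.

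**6. Precision at n = 53.** Fisher z with SE = 1/√50 = 0.141, so the half-width is 1.96 × 0.141 = 0.277.

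- r = 0.35: z = 0.365, limits 0.088 and 0.643, giving 0.09–0.57.
- r = 0.60: z = 0.693, limits 0.416 and 0.970, giving 0.39–0.75.

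The two intervals overlap from 0.39 to 0.57. An estimate of 0.35 is still compatible with the lowest pilot value of 0.49.

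**The case against.** Several points on the other side are sound.

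- **The stated reason is not reversed.** A reader might infer that a longer average and a controlled diet can only raise correlations, so that the article's reason points the wrong way. The documents do not support this. The seven-product average contained the tested product, and moving to 378 meals removes nearly all of that overlap, which lowers the typical correlation. The RepEAT average also covers lunch, snacks and self-chosen items as well as breakfast and dinner, and such a varied average may track any one product less closely. The explanation is incomplete, not wrong in direction.
- **There is no contradiction with the pilot.** The article reports the pilot range and openly departs from it. At n = 27 the approximate 95% CI for 0.49 is 0.14–0.73, which includes 0.3–0.4.
- **The assumption is conservative.** For a test of r = 0 it enlarges the study.
- **Repeatability is examined.** Section 1 (Introduction) asks about responses that recur, and sections 3 and 5 plan to compare the three repeats, so poor reliability would become visible.

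The last point is the strongest, but it does not close the gap. Nothing in sections 2.4, 3 or 5 ties the repeats to the rule for reading a low correlation. The article states that rule itself, so it is not a detail left to a fuller document.

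**Conclusion.** The point holds in this form. The sample size supports rejection of r = 0, which is not the finding the study wants to make, and the rule that a low correlation is person-specific does not allow for noise. With no person-specific response, r = 0.3–0.4 needs only a single-response reliability of 0.09–0.16. This assumes a near error-free average and one response per product; the article does not say whether the repeats are averaged before correlating.

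The step from 0.49–0.85 to 0.3–0.4 is unquantified. Under equal variances and equal intercorrelations the pilot range projects to about 0.34–0.82, so only the weakest pilot product fits.

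A reader might also infer that the study is underpowered because its effect size is unsupported. For the stated test this does not follow, since pilot-like values would need only 6–27 participants. What limits the answer is the precision of each correlation at n = 53, which the article does not give.

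**What to change.** 1. Label 0.3–0.4 as a planning assumption. The reason given for expecting lower values can stay; add that the pilot average contained the tested product.
2. Restate the justification as precision: the 95% CI of a product–average correlation at n = 53 across plausible values, for example about 0.09–0.57 at r = 0.35 and 0.39–0.75 at r = 0.6.
3. Compute each correlation with the product left out of its own average. Do the same for the pilot if its data are to hand, where the overlap matters most.
4. Replace the rule for a low correlation. Estimate R for each product from the three repeats and take as the ceiling √R for a single response, or √(3R/(1 + 2R)) for the mean of three. Call a correlation low only if it falls clearly below that ceiling, or report r/√(reliability) with an interval. Do not judge it against zero.

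The cost is one rewritten paragraph in section 2.4, a sentence or two in section 3 and a small change to the analysis code. No new participants or measurements are needed. Section 2.1 puts the project at data cleaning, so the rule can still be fixed before the correlations are examined. The change should be dated and described as made after data collection.
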